### Efficacy Analysis

#### Primary efficacy analysis

LPFS is defined as the time from date of randomisation to local recurrence or death from any cause in the absence of documented local disease progression. LPFS will be censored on the date of the last tumour assessment on study for patients who do not have local tumour progression and who do not die while on study.

A log-rank test (two-sided) will be used to compare LPFS between the two treatments. The LPFS-rates will be derived from the Kaplan Meier estimate [22] and the confidence intervals will be calculated using Greenwood's formula.

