## Background

Chordomas (1 - 4% of all malignant bone tumors) of the skull base are relative rare lesions of the bones. The incidence is around 100 new cases per year in Germany and 0.08/100000 in the US corresponding to around 300 new cases per year [1]. Chordomas arise from embryonic remnants of the notochord and are found at the base of the skull area in 35% of all cases. According to the histopathological findings, chordomas are divided into conventional (most common), chondroid and dedifferentiated types [2,3]. Histological differentiation between chordomas and chondrosarcomas is difficult and must contain immunhistochemical tests [4]. Chordoma is immunopositive for epithelial markers like cytokeratin and endothelial membrane antigen (EMA), whereas chondrosarcoma is negative for both. Both chordomas and chondrosarcomas can be positive for S-100 and vimentin.

The average age at the diagnosis is 49 years for base of skull localization. Also, the base of the skull is the most common localisation of chordomas in children and adolescents. In children and adolescents chordomas may behave more aggressively [5]. Men are affected more frequently than women.

Surgical resection is the primary treatment standard, though complete resection is nearly impossible due to close proximity to critical and hence also dose limiting organs for radiation therapy i.e. optic nerves, chiasm and brainstem. Level of recurrence after surgery alone is with reported rates between 50% and 100% [6] comparatively high, so adjuvant radiation therapy is very important for the improvement of local control rates in the primary treatment even after complete resection. Tumour volume is an important prognostic factor, hence a tumour debulking is usually required before radiation therapy application [7]. Other prognostic relevant risk factors are the histological tumour type, resection status, gender, and the age of the patient [8,9].

Radiation resistance is a common characteristic of chordomas [10,11], so high total doses are needed to achive acceptable local control rates after radiotherapy. Conformal precision and image guided radiation therapy techniques provide a safe technique for dose escalation [12]. The physical characteristics of carbon ions or protons such as inverted dose profile allow steep dose gradients and therefore provide further benefit in this field by potentially reducing toxicity.

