### Risk group definition

Secondary objectives of the study will be explorative analysed also according to risk groups mentioned in Table 1.

**Table 1 T1:** Risk group characterization

Low-risk	High-risk
Age > 30 years	Age ≤ 30 years
Male chordoma	Female chordoma
No OAR compression	Compression of OAR
Primary tumour	Recurrent tumor
Tumour size < 70 ml	Tumour size > 70 ml

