### Randomisation

The randomisation will be done using the on-line randomisation tool (Randomizer.at) which is self-serve and runs exclusively on the Internet. An on-screen form with patient details will be completed. The treatment allocation will be immediately notified. The randomisation will be performed regarding treatment arms A and B. Stratification parameters include the following criteria: age (< 30, ≥ 30 years) and gender.

As this is an open-label study there will be no blinding of treatment assignment.

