### Sample Size Determination

The sample size is calculated on the basis of the following assumptions:

• LPFS rate 5 years after radiation therapy of 70% 1) for proton therapy, hazard λ_1 _= 0.0713, and 80% for carbon ion therapy, hazard λ_2 _= 0.0446 (hazard ratio = 1.599).

• Recruitment period of 5 years, with constant accrual rate of 20% patients per year and a follow-up time of 8 years.

• One interim analysis according to a group sequential design with two stages.

Formula of Schoenfeld [20,21] used for the calculation of the number of accumulated events. For a two-sided logrank test with an overall two-sided significance level of 0.05 (including interim and final analyses) and power of 0.80, 143 events are required. The critical values and the test characteristics of the group sequential test design were calculated for an O'Brien and Fleming type alpha spending function. The computation assumes equal allocation to the two groups (n_2_/n_1 _= 1). Assuming an accrual time of 5 and a maximum observation time of 13 years a total of 319 patients is expected to yield the necessary number of events if the accrual rate is constant. Under these assumptions, the time point of the interim analysis should be 7 years after the first patient is entered. The ADDPLAN, Version 4.0 calculator was used for the sample size estimation. With the assumption that approximately 7% of the patients will be lost to follow-up a total of 344 patients will be needed to accumulate 143 events.

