#### Secondary efficacy analyses

A sensitivity analysis will be performed on the primary efficacy endpoint to assess the impact of protocol deviations using the per protocol analysis set.

A hazard ratio with 95% confidence interval for the experimental arm relative to control arm will be estimated by proportional hazard regression [23-25] with treatment, gender, age (< 30, ≥ 30 years), tumour size (< 70 ml, ≥ 70 ml), compression of OAR (yes/no) as covariates. A logistic regression analysis [26] will be carried out to identify relevant prognostic factors. Benefit from intervention (yes or no) will be defined as belonging to the patients groups (low-risk, high-risk group) which lay above the 50% percentile of LPFS.

The analyses of OS, PFS and metastasis free survival will be conducted using log-rank test. The Kaplan-Meier method will be used to obtain the estimates of the survival functions and the 95% confidence intervals will be estimated using Greenwood's formula. Covariates will not be included in the calculation.

All of these secondary analyses will be conducted at the 0.05 level of significance.

Descriptive statistics will be provided for all other secondary endpoints. Additional exploratory analyses will be used as appropriate. Generally, results will be given by summaries of the data as indicated above together with the test statistics and their associated p-values. Appropriate confidence intervals of estimates of effect will be given to quantify the degree of uncertainty of the point estimates.

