### Interim Analysis

There is one planned interim analysis. The purpose for performing the interim analysis is to support a possible early detection of the superior therapy. In case of reaching a critical value of 2.9626 in the interim analysis the underlying therapy should neither be used for any further patients treated within the study nor for any patients outside of the study.

The interim analysis will be performed as soon as 50% of the expected events have occurred. Assuming that rate of recruitment proceeds at the rate estimated for this study the time of the interim analysis will be approximately 7 years after the first patient is entered. This time point is after the end of recruitment. For this reason the interim analysis does not have the goal to stop the study early and should not define a critical value of early stopping for futility. Independent of the result of the interim analysis the study should continue as planned with the recruited and already treated patients.

Interim statistical hypothesis tests will be performed only for the primary efficacy endpoint, LPFS. The log-rank test identical to the primary analysis will be performed at the scheduled interim analysis and compared to group sequential boundary based on the current information time. The LPFS curve estimated by the method of Kaplan-Meier will be summarized for each treatment group. The hazard ratio will also be estimated. The interim safety report will review all aspects of the data collected for each subject. Other important additional factors that reflect the integrity of the protocol will be addressed in the interim report.

A group sequential design with an O'Brien and Fleming alpha spending function is used to control the type I error. The nominal one-sided significance level for the interim analysis determined by using the O'Brien-Fleming stopping rule is 0.0015.

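### Randomisation is stratified by age and gender, but the log-rank tests name no strata; if the factors are prognostic this costs some power, while validity is unaffected

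*Protocol article*

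**What the plan says.** Under Randomisation, the protocol article sets the strata: "Stratification parameters include the following criteria: age (< 30, ≥ 30 years) and gender". The Background gives the reason to expect these to matter: "Other prognostic relevant risk factors are the histological tumour type, resection status, gender, and the age of the patient". Table 1 uses both again to separate low-risk from high-risk patients.

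The tests are described without strata:

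- Primary efficacy analysis: "A log-rank test (two-sided) will be used to compare LPFS between the two treatments".
- Interim Analysis: "The log-rank test identical to the primary analysis will be performed at the scheduled interim analysis".
- Sample Size Determination: a two-sided log-rank test at an overall level of 0.05 across both analyses, again with no strata.
- Secondary efficacy analyses, on the log-rank tests of overall, progression-free and metastasis-free survival: "Covariates will not be included in the calculation".

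Age and gender enter only one named analysis, the secondary proportional hazards model, fitted "with treatment, gender, age (< 30, ≥ 30 years), tumour size (< 70 ml, ≥ 70 ml), compression of OAR (yes/no) as covariates".

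**The concern.** Stratified randomisation removes most of the chance imbalance between arms in age and gender. If these factors affect local-progression free survival (LPFS), the numerator of the log-rank statistic then varies less from trial to trial than it would under simple randomisation. The unstratified variance does not take credit for this, so the statistic is a little too small. Mixing strata with different hazards also pulls the overall treatment contrast that the test sees slightly towards the null.

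At stake is efficiency. A test that ignores prognostic strata can run below its 5% level and lose power that the stratified randomisation could have delivered. The design has almost no reserve, as the working shows, and events are hard to come by in a rare tumour treated at one centre.

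**Working it through.** **1. The plan's own figures.** From Sample Size Determination: 5-year LPFS of 70% and 80%, hazard ratio 1.599, two-sided alpha 0.05, power 0.80, 5 years of accrual, 13 years of maximum observation and 7% loss to follow-up.

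- Events (Schoenfeld, 1:1): D = 4(1.960 + 0.842)² / (ln 1.599)² = 142.5, so 143.
- Interim at 50% of events with O'Brien-Fleming type spending: critical value 2.9626, one-sided level 0.0015. The final critical value is 1.969, and group sequential power at 143 events is 0.799.
- Event probability per arm: 1 − [exp(−8λ) − exp(−13λ)] / (5λ). With λ = 0.0713 and 0.0446 the average is 0.449, and 143 / 0.449 gives 319 patients.
- Loss to follow-up: 319 / 0.93 = 343.01, so 344.

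Everything reproduces for a plain log-rank test.

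**2. The two tests.** With gⱼ the arm indicator (1 = carbon) of the patient with event j, and pⱼ the proportion on carbon among those then at risk, U = Σ(gⱼ − pⱼ), V = Σpⱼ(1 − pⱼ) and Z = U/√V. The unstratified test takes the risk sets over all patients. The stratified test computes U and V within each of the four age-by-gender cells, and Z = ΣU/√ΣV.

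**3. Simulation.** 319 patients; permuted blocks of 4 within cells (assumed); exponential times with control 5-year LPFS calibrated to 70% overall; a single look at 1.96. There were 10,000 runs under the null and 6,000 under each alternative. The prognostic hazard ratios and the shares under 30 and female are assumed. The treatment effect was set in two ways: a hazard ratio of 0.626 within every stratum, or 5-year LPFS of 80% on carbon overall (which needs a within-stratum ratio from 0.626 down to 0.600). Each cell shows unstratified / stratified.

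| Assumed HR, age <30 / female | Share <30 / female | Size | Power, 0.626 within strata | Power, 80% overall |
|---|---|---|---|---|
| 1 / 1 | 10% / 45% | 0.049 / 0.049 | 0.788 / 0.789 | 0.796 / 0.794 |
| 1.5 / 1.2 | 10% / 45% | 0.046 / 0.046 | 0.796 / 0.796 | 0.792 / 0.792 |
| 2 / 1.5 | 10% / 45% | 0.047 / 0.048 | 0.775 / 0.786 | 0.781 / 0.796 |
| 2 / 1.5 | 20% / 50% | 0.043 / 0.051 | 0.774 / 0.794 | 0.781 / 0.805 |
| 2 / 2 | 20% / 50% | 0.040 / 0.051 | 0.758 / 0.787 | 0.788 / 0.818 |
| 3 / 2 | 20% / 50% | 0.033 / 0.045 | 0.720 / 0.783 | 0.763 / 0.819 |
| 3 / 3 | 20% / 50% | 0.028 / 0.049 | 0.686 / 0.784 | 0.761 / 0.843 |

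The Monte Carlo standard error is √(0.05 × 0.95 / 10,000) = 0.002 for size and √(0.8 × 0.2 / 6,000) = 0.005 for power. In the first three rows the unstratified size cannot be told apart from 0.05 with any confidence; from the fourth row on it is clearly lower.

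**4. Further strong scenarios.** For age/female hazard ratios of 2.5/2.0 and 3.0/2.5, with 0.626 within strata (3,000 runs each, 12-20% under 30 assumed), power was 75.1% against 79.2% and 70.0% against 78.0%: losses of 4.1 and 8.0 points. Calibrated to 70% against 80% overall (12% under 30 and 45% female assumed), it was 78.0% against 81.2% and 76.4% against 82.1%: losses of 3.2 and 5.7 points.

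**The case against.** The case for leaving the text alone has real substance.

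- **The primary test is unstratified only by inference.** A stratified test is also a log-rank test, the article condenses a longer protocol, and it leaves analysis details to a statistical analysis plan that is not shown. The explicit exclusion of covariates concerns the secondary endpoints, not LPFS. This stands as a caution. Yet the article names the primary test, repeats it for the interim and the sample size, and lists age and gender where it wants them, so an unstratified test remains the natural reading.
- **The size of the loss is not known.** This stands in full. With weak factors there is nothing to gain, and the lowest power figures depend on fixing 0.626 within strata rather than the overall rates of 70% and 80% from which the plan derives its hazard ratio.

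A reader might also infer more than the documents support:

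- *That the reported hazard ratio will be attenuated.* The Cox model for the final estimate already includes both stratification factors. Only the model for the interim hazard ratio is left open.
- *That the error rate or the sample size is wrong.* The departure is in the conservative direction, so a positive result would stand, and all the sizing figures reproduce.
- *That the Cox model is deficient because Table 1 also lists "Recurrent tumor" and the model omits it.* That item is not a stratification factor and has no bearing on the primary test. Table 1 serves exploratory analyses and does not oblige the model to carry every entry.

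**Conclusion.** The mismatch between the stratified randomisation and the tests as described is real, and its direction is clear: if age and gender are prognostic, as the protocol says, the unstratified test is somewhat conservative and less powerful. The loss is about 0 points of power for weak effects, 1 to 3 points for assumed hazard ratios of 1.5 to 2, and roughly 3 to 10 points only for strong effects, depending on calibration. In the strongest cases the actual level falls to about 0.03. Across the same scenarios the stratified test keeps its level near 0.05 and its power at about 0.78 or more.

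These figures rest on assumed prognostic effects, age and gender shares, block size and a single look. This is an improvement in efficiency and consistency, worth making because it is nearly free. It is not a flaw in validity.

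**What to change.** State that the primary and interim LPFS comparisons use a two-sided log-rank test stratified by age group (<30, ≥30 years) and gender. Do the same for overall, progression-free and metastasis-free survival, and amend the sentence that excludes covariates there. Add a rule, fixed before any comparison by arm, for pooling sparse cells: splitting the under-30 group by gender may leave very few events, so the rule should say when those cells are merged, judged on counts with the arms combined. Keep the unstratified test as a sensitivity analysis.

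The adjusted Cox model, the 143 events, the 319 and 344 patients and the 2.9626 boundary need no change. The cost is a few sentences. Both factors are already recorded at randomisation, and in the simulations stratifying cost essentially nothing when they were not prognostic. If the analysis plan already specifies strata, only the protocol wording has to be brought into line.

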#### Secondary efficacy analyses

A sensitivity analysis will be performed on the primary efficacy endpoint to assess the impact of protocol deviations using the per protocol analysis set.

A hazard ratio with 95% confidence interval for the experimental arm relative to control arm will be estimated by proportional hazard regression [23-25] with treatment, gender, age (< 30, ≥ 30 years), tumour size (< 70 ml, ≥ 70 ml), compression of OAR (yes/no) as covariates. A logistic regression analysis [26] will be carried out to identify relevant prognostic factors. Benefit from intervention (yes or no) will be defined as belonging to the patients groups (low-risk, high-risk group) which lay above the 50% percentile of LPFS.

The analyses of OS, PFS and metastasis free survival will be conducted using log-rank test. The Kaplan-Meier method will be used to obtain the estimates of the survival functions and the 95% confidence intervals will be estimated using Greenwood's formula. Covariates will not be included in the calculation.

All of these secondary analyses will be conducted at the 0.05 level of significance.

Descriptive statistics will be provided for all other secondary endpoints. Additional exploratory analyses will be used as appropriate. Generally, results will be given by summaries of the data as indicated above together with the test statistics and their associated p-values. Appropriate confidence intervals of estimates of effect will be given to quantify the degree of uncertainty of the point estimates.

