So far, proton therapy is the gold standard in treatment of rare skull-base tumours like chordoma and low grade chondrosarcoma. The Loma Linda University Medical Center (LLUMC) [13] and the Massachusetts General Hospital (MGH) in Boston [14] have the largest experience in particle therapy for these entities. 3-year local control for chordomas after fractionated proton radiation therapy in 33 patients at LLUMC was 67% and the actuarial 5 year survival rate was 79% respectively [14]. The outcome of 519 cases of chordomas and chondrosarcomas of the skull base including 290 chordomas treated with a combination of proton and photon therapy at MGH/HCL shows a significant difference in local control and survival rates between the patients with chordoma and chondrosarcoma. 5- and 10-year local progression free survival was 98% and 94% for chondrosarcomas and 73% and 54% for chordomas [13,14].

Proton therapy results from PSI in Villingen, Switzerland were published by Weber et al. and showed 3 year local control rates of 87.5% for chordomas. However, the treated tumour volumes with a median GTV of 16.4 ml were relatively small. 29 patients, among them 18 patients with chordoma were treated to a median target dose of 74 GyE. The 3-year actuarial PFS rate for the entire patient cohort was 90% [15].

Carbon ions though, have a higher biological effectiveness than either protons or photons, which might improve the results of these radio-resistant tumours [16]. Carbon ion therapy is available only at the National Institute of Radiological Sciences (NIRS) in Japan and up to July 2008 has been available at the Gesellschaft für Schwerionenforschung (GSI) Darmstadt in Germany. The experience of our Japanese colleagues is limited to 40 patients with chordoma and chondrosarcoma of the skull base who could be treated effectively and without serious side effects [17]. NIRS beam delivery technique relies on passive scanning necessitating various modulators to adjust for treatment depth and tissue inhomogeneities within the beam path.

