### Secondary objectives of the study

1. Assessment of overall survival, progression free and metastasis free survival, patterns of recurrence, local control rate and morbidity.

2. Prognostic factors, definition of patients who will benefit from the adjuvant therapy, risk group definition.

3. Plan quality (target coverage, sparing of organs at risk, integral dose).

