### Treatment planning examinations/Target definition

The treatment planning CT (obligate native CT, CT with contrast facultative) and MR - Examination (MRT - compulsory sequences - axial T1 post gadolinium and T2 fat saturated or Flair) will be performed in treatment position using the immobilisation device and will be co-registered. The treatment planning CT will consist of continuous 3 mm slices obtained in a stereotactic or virtual simulation set-up.

The delineation of organs at risk and target volume definition will be done on the basis of CTs and MRI scans. The PTV1 should include the GTV (entire residual tumour) and a 1-2 mm safety margin. PTV2 includes the PTV1 with individual safety margin based on surgical and histological reports, and MR-images to account for subclinical disease. The PTV2 includes the whole clivus and the prevertebral muscles down to the basis of the second cervical vertebra in any case. Normal tissue constrains will be defined as follows: eyes, optic nerves, chiasm, brainstem, spinal cord obligatory, temporal lobes, mandible, salivary glands and others facultatively. An overlap of the PTV and the OAR needs to be avoided.

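### The only specified Cox model enters age and tumour size as two-category covariates, which loses prognostic information if their effects are smooth; the cost to the treatment hazard ratio is small

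*Protocol article*

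**What the plan says.** Under Secondary efficacy analyses, the protocol article specifies one proportional hazards model. Its purpose is the hazard ratio of carbon ions against protons with a 95% confidence interval, and it is fitted "with treatment, gender, age (< 30, ≥ 30 years), tumour size (< 70 ml, ≥ 70 ml), compression of OAR (yes/no) as covariates". The next sentence gives the search for prognostic factors to a logistic regression and does not state its covariates or their coding.

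Other places bear on the choice:

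- Secondary objectives of the study, item 2: "Prognostic factors, definition of patients who will benefit from the adjuvant therapy, risk group definition".
- Background: "Tumour volume is an important prognostic factor, hence a tumour debulking is usually required before radiation therapy application". The same paragraph lists the patient's age among the other prognostic factors.
- Randomisation: age below 30 against 30 and over is a stratification factor, with gender.
- Risk group definition, Table 1: 30 years and 70 ml are also risk-group limits, for exploratory use. The high-risk categories there are age ≤ 30 years and size > 70 ml.
- Treatment planning examinations/Target definition: "The PTV1 should include the GTV (entire residual tumour) and a 1-2 mm safety margin", so the GTV is contoured for every planned patient.
- Organization, Workflow and Follow-up: date of birth and dose-volume data are recorded.

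**The concern.** Both variables can be had on their natural scale. A 70 ml cut cannot even be applied unless the volume in ml, or something close to it, is known. With the coding as written, the model treats a 5 ml and a 65 ml residual tumour as equal, and likewise a 31-year-old and a 79-year-old.

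The cuts also appear to lie away from the centre of the distributions. The Background gives an average age at diagnosis of 49 years for this site. The only tumour volume in the document comes from another centre, where "the treated tumour volumes with a median GTV of 16.4 ml were relatively small". The document nowhere claims that risk jumps at 30 years or at 70 ml.

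What is at stake is how well the model describes and adjusts for two named prognostic factors. The validity of the primary comparison is not in question.

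**Working it through.** **1. The plan's own figures.** Sample Size Determination states "power of 0.80, 143 events are required". Schoenfeld's formula with 1:1 allocation and a hazard ratio of 1.599 gives

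events = 4 × (1.960 + 0.842)² / (ln 1.599)² = 142.5, so 143.

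The two-look O'Brien-Fleming spending design gives 143.0. With entry uniform over 5 years and 13 years in total, the probability of an event in an arm with hazard λ is 1 − (e^(−8λ) − e^(−13λ))/(5λ). For λ = 0.0713 and 0.0446 the mean is 0.4487. Then 143/0.4487 = 318.7, so 319, and 319/0.93 = 343.01, so 344. All three figures reproduce. None of them uses the covariates.

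**2. Information kept by a cut.** For a covariate with a linear effect on the log hazard, the share of information kept is the squared correlation between the cut variable and the continuous one. For a normal covariate with a fraction p beyond the cut at standardised value z, this is φ(z)²/(p(1−p)). For a uniform covariate it is 3p(1−p).

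*Age, cut at 30.* The mean of 49 is from the Background and the range 18-80 from the inclusion criteria. The shape and SD are assumed.

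| Assumed shape | Share under 30 | Information kept |
|---|---|---|
| Truncated normal, SD 12 | 5% | 22% |
| Truncated normal, SD 15 | 9% | 30% |
| Truncated normal, SD 18 | 11% | 35% |
| Uniform on 18-80 (mean 49) | 12/62 = 19% | 3 × 0.194 × 0.806 = 47% |

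In the truncated normal cases about 18 to 39 of 344 patients would be under 30 (0.052 × 344 and 0.113 × 344).

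*Tumour volume, cut at 70 ml.* A log-normal shape is assumed, with a median from 16.4 ml (the one cited figure) to 70 ml and an SD of log volume from 0.7 to 1.3. Here z = ln(70/median)/SD.

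| Median | SD of log | Share ≥ 70 ml | Information kept |
|---|---|---|---|
| 16.4 ml | 0.7 | 2% | 12% |
| 16.4 ml | 1.3 | 13% | 40% |
| 30 ml | 1.0 | 20% | 49% |
| 50 ml | 1.0 | 37% | 61% |
| 70 ml | any | 50% | 64% |

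First row: z = 1.451/0.7 = 2.07 and p = 0.019, so the share is 0.0465²/(0.019 × 0.981) = 0.12. Last row: 0.399²/0.25 = 0.64.

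**3. What this does to the model.** Simulation used the plan's hazards, 344 patients, 5-year accrual, a 13-year cut-off, 1,500 runs per scenario and about 156 to 158 events. The cuts isolated 20% of patients on volume and 10% on age. Effects are log hazard ratios per SD.

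| True effect (volume, age) | Treatment power, continuous / cut | Volume power, continuous / cut | Age power, continuous / cut |
|---|---|---|---|
| Smooth, 0.235 and 0.235 | 83.6% / 82.8% | 81% / 57% | 82% / 45% |
| Smooth, 0.4 and 0.3 | 83.1% / 80.1% | 99.9% / 94% | 96% / 67% |
| Step at the cut | 81.7% / 82.9% | 57% / 87% | 48% / 92% |

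With smooth effects, cutting costs the treatment test 0.8 and 3.0 points. The Monte Carlo standard error of each single figure is about 1 point (√(0.83 × 0.17/1500) = 0.0097). The covariate tests lose much more. With a step at the cut, the covariate comparison reverses.

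**4. Boundary signs.** Table 1 counts age ≤ 30 as high-risk, while the Cox model puts a 30-year-old in the ≥ 30 category. Table 1 splits size into < 70 and > 70 ml, which leaves exactly 70 ml unassigned. The model uses ≥ 70 ml.

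**The case against.** The strongest defence is that this Cox model is not there to find prognostic factors. It estimates an adjusted treatment hazard ratio, and for that the coding barely matters. The identification of prognostic factors belongs to the logistic regression. A reader might infer that the cuts cost the prognostic-factor objective some 20 to 45 points of power. The document does not support this: it does not say that prognostic factors will be judged from the Cox coefficients, and it does not state the coding of the logistic model. This part of the defence stands in full.

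The 30-year cut also has a reason. It is the randomisation stratum, and adjusting for a stratification factor as it was stratified is standard. That stands, and it is why the stratum should stay. It gives no reason to leave out age in years, and it does not cover tumour size, which is not a stratification factor.

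Age risk may not be monotone: the Background mentions more aggressive behaviour in the young, and LPFS counts death from any cause. That tells against a single straight line in age, but a spline meets it.

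Finally, tumour volume in ml is not listed as a data item, and the 16.4 ml median comes from another centre's series of 29 patients, 18 of them with chordoma. Availability is therefore implied by contouring, and how far out 70 ml lies in this trial is unknown. The wide volume range above reflects this.

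The plan's allowance for additional exploratory analyses permits continuous modelling but does not pre-specify it. The coding is stated in the article, so it is not a detail left to the SAP.

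**Conclusion.** The point holds as a modest matter of efficiency. Two covariates that the document itself calls prognostic enter the only specified Cox model as two categories. If their effects are smooth, the cuts keep about 22-47% of a linear age effect and about 12-64% of a log-linear volume effect. These ranges rest on assumed shapes and spreads, since the document gives only a mean age and one outside median volume. If the true effect is a step at the cut, nothing is lost and the cut coding does better.

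For the adjusted treatment hazard ratio the cost is about 1-3 points of power. The primary log-rank test, the 143 events and the 344 patients are untouched.

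It is also tempting to say that at least a third of the information is always lost. That is not a general bound: a uniform covariate cut at its median loses 25%, and a step effect loses none.

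**What to change.** In Secondary efficacy analyses, enter log tumour volume and age in years as continuous terms in the Cox model, each as a restricted cubic spline with 3 knots. Retain the <30/≥30 age stratum as the randomisation factor. State the same continuous coding for the prognostic-factor model. Keep the Table 1 cuts for descriptive risk-group tables, and reconcile their boundary signs with those in the model text.

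The cost is a sentence or two of wording. No new measurement is needed, provided the contoured GTV volume is recorded in ml. A 3-knot spline uses one more degree of freedom than a two-category term. Age uses a further one if the stratum is kept as a coefficient and not as a stratum of the baseline hazard. A spline or a per-doubling hazard ratio also reads less directly than a two-group contrast, which the Table 1 groups would still supply descriptively.
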